### Adherence and protocol deviations

Since the intervention is deployed on a group basis rather than individually, adherence definitions will take account of this. Standard adherence will be defined as the intention to treat a cluster of residences with ATSBs, as randomized. Individual adherence will be defined based on ATSBs present at individuals’ households. Both individual and cluster-level adherence measures will be defined and pre-categorized prior to final analysis and used to categorize the per-protocol trial population.

The per-protocol analysis populations will be defined as those living in intervention clusters where ATSB was deployed and replaced according to the planned schedule. Clusters where more than 1-month delay in ATSB deployment occurred or where substantial deployment of ATSB into control areas occurs (e.g., deployment consistent with distribution of ATSB to control areas) will be removed from the per-protocol analysis population.

Standard protocol deviations will be considered reportable/summarizable when clusters refuse placement of ATSB or have been treated/not treated contrary to their randomization assignment and providing initial study consent. Additionally, protocol deviations will be considered to have occurred if ATSB replacement visits for an entire cluster by the study team are delayed by more than 3 weeks from the expected timeline according to study planning.

Protocol deviations related to failure to deliver or replace ATSB will be summarized in the final trial reports as well as incorporated into the calculation of adherence.

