### Analysis populations

There are two analysis populations for the primary outcome assessment: These are the intention-to-treat population and the per-protocol analysis population. The intention-to-treat population consists of all eligible individuals recruited and consented to participate in the study. The primary analysis will be conducted on the intention-to-treat population. Per-protocol analysis populations will be those eligible, recruited, and consented individuals whose adherence at cluster level meets the adherence standard. Additional household-level per-protocol analysis may be conducted consisting of ATSB deployment at the household level consistent with randomization assignment.

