## Analysis

### Outcome definitions

The primary outcome measure is the incidence rate of clinical malaria cases assessed among people aged 12 months to less than 15 years (≥ 5 to 15 in Mali). A clinical case is defined as having an axillary temperature of ≥ 37.5 °C or self-reported fever within the past 48 h, plus a positive malaria RDT. Incidence rate is defined as the total number of incident malaria cases divided by the total person-time observed among each cohort. Outcome assessment will be conducted on each cohort participant monthly. As malaria treatment drugs will be administered to all positive clinical cases (fever + positive RDT) after monthly case ascertainment, each positive (treated) participant will have 2 weeks of the following month of observation time subtracted from their at-risk person-time to account for the prophylactic effect due to sustained antimalarial drug concentration and hence not being at risk of infection. In individuals who are symptomatic and have a positive RDT test in the month following a positive diagnosis of malaria via RDT and treatment, a positive RDT in the following month may indicate persistence of antigen in the blood after effective treatment rather than true reinfection. In such cases, PCR or microscopy results for a *Plasmodium falciparum* infection will be used to resolve if the positive RDT is a result of persistent antigenemia or a true infection (reinfection/recrudescence). In Mali, only microscopy will be used to resolve such cases. In Kenya and Zambia, PCR results will be used where available, and otherwise microscopy. Where the RDT and either the PCR or microscopy results are both positive in month two and the patient meets the other clinical criteria (patent fever or history of fever in the previous 48 h), these observations will be treated as new clinical cases. To keep field procedures unambiguous, a blood slide will be taken whenever a positive RDT is recorded in Mali. Temporary absences from the study area not resulting in failure to ascertain monthly outcomes will not be considered as reducing individual exposure time. Absences greater than the testing interval (1 month ± 5 days) and/or resulting in the failure to ascertain a monthly test result will be removed from the exposure time—meaning that exposure will only be considered to start 1 month prior to the most recent test result.

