## Missing data

### Missing outcome data

Significant effort will be made to reduce missing outcome data by revisiting cohort households multiple times and pre-scheduling follow-up visits where possible. When missing data does arise due to failed monthly outcome assessment, no imputation will be used. Missing outcomes due to participant absence will result in censoring (removal of the previous period of follow-up time if there is a missing outcome). They will also have 2 weeks of the next period follow-up time removed as per the definition of the primary outcome. Two sensitivity analyses will be carried out for the primary outcome. These will be the last observation carried forward (e.g., an assumption that a clinical malaria case identified at the last time point observed would represent subsequent new clinical cases (and follow-up time removal) at each missing time point or that the absence of a clinical case at last observation would indicate no clinical cases observed at any missing time points and full follow-up time). This analysis is consistent with a true intention to treat protocol. A second sensitivity analysis will be to assume that all missing values would have resulted in negative findings thus imputing zero extra unobserved clinical cases across both study arms and assuming full follow-up time. These analyses will only be applied to the intention-to-treat analysis population because the per-protocol study population already assumes that full follow-up (all outcome assessments) occurred. Full reporting of the fraction of missing outcome assessments by study arm will be conducted for the intention-to-treat study population.

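### The two missing-outcome sensitivity analyses do not test missingness that depends on the unseen outcome, and the per-protocol set is exempted on a premise its definitions do not contain

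*SAP article*

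**What the plan says.** Under Missing outcome data, the primary analysis imputes nothing; the interval before a missed assessment is taken out of person-time. Two sensitivity analyses follow.

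- **Carry-forward.** The last observed status is repeated at every missed visit. For a child last seen as a case this means "an assumption that a clinical malaria case identified at the last time point observed would represent subsequent new clinical cases", with follow-up time removed each time. For a child last seen without malaria it means no cases and full follow-up. The plan presents this as faithful to intention to treat.
- **All-negative.** Every missed visit counts as no case, "imputing zero extra unobserved clinical cases across both study arms and assuming full follow-up time".

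Both are confined to the intention-to-treat population, "because the per-protocol study population already assumes that full follow-up (all outcome assessments) occurred".

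The per-protocol set is defined elsewhere. Adherence and protocol deviations says: "The per-protocol analysis populations will be defined as those living in intervention clusters where ATSB was deployed and replaced according to the planned schedule". Analysis populations says: "Per-protocol analysis populations will be those eligible, recruited, and consented individuals whose adherence at cluster level meets the adherence standard", and allows an additional version based on deployment at the household.

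Outcome definitions says that every case is treated, that two weeks of person-time are then removed, and that a symptomatic positive RDT in the month after a treated case is a new case only if PCR or microscopy (microscopy only in Mali) confirms it.

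**The concern.** The trial is open-label and uses no sham stations, so attendance could differ between arms for reasons linked to illness. A sensitivity analysis should show how far the result depends on what happened in the missed months. If the two planned analyses agree with the primary result for purely arithmetical reasons, the report will claim a robustness that was not examined. If they disagree because attendance merely differed in amount, they will raise a false alarm.

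Carry-forward also fits the endpoint poorly. A malaria episode is acute, treated and recurrent, yet the rule turns one treated episode into a fresh case at every missed visit.

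Finally, an analyst cannot build the per-protocol set from the three sections together. Either the exemption has no basis, or there is an unstated complete-attendance requirement, which would select children on behaviour after randomisation.

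**Working it through.** **1. Per-protocol set.** Adherence and protocol deviations uses ATSB deployment and replacement, and excludes clusters with a delay of more than one month or with substantial deployment into control areas. Analysis populations uses cluster-level adherence, optionally household-level. Neither mentions completed outcome visits. Missing outcome data nevertheless says that "the per-protocol study population already assumes that full follow-up (all outcome assessments) occurred". The sections conflict.

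**2. All-negative analysis, by algebra.** Let C be observed cases, T planned person-time and m the missing share in an arm (1 = ATSB, 0 = control). Ignoring the small two-week removals, the primary rate is C/[T(1−m)] and the all-negative rate is C/T. Hence

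IRR(all-negative) ≈ IRR(primary) × (1−m1)/(1−m0).

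The case rate in the missed months does not appear. Examples of the factor: 1.00 for 20% missing in both arms; 0.88 for m0 = 15%, m1 = 25%; 1.29 for m0 = 30%, m1 = 10%.

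**3. Simulation.** Inputs: 12 monthly visits, control case probability 0.50/6 = 0.083 per month (Zambia, Table 2), half a month removed after each case, large samples so that differences are bias rather than noise. The missingness patterns are assumptions, not figures from the plan.

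| Assumed pattern | Missing, control / ATSB | True IRR | Primary | Carry-forward | All-negative |
|---|---|---|---|---|---|
| A. Random, equal | 18.3% / 18.3% | 0.69 | 0.693 | 0.691 | 0.693 |
| B. 40% of ATSB-arm case visits missed, totals equal | 18.3% / 18.2% | 1.00 | 0.767 | 0.767 | 0.769 |
| C. As B, with a true effect | 18.3% / 18.5% | 0.69 | 0.537 | 0.535 | 0.535 |
| D. ATSB-arm visits missed: 40% of case visits, 25% of others; control 15% | 13.7% / 24.1% | 1.00 | 0.827 | 0.829 | 0.728 |
| E. Random, more in control | 27.5% / 9.2% | 0.69 | 0.699 | 0.692 | 0.875 |
| F. Random, more in ATSB | 9.2% / 27.5% | 0.69 | 0.690 | 0.693 | 0.551 |
| G. Control visits missed 50% of the time after a treated case | 20.2% / 18.3% | 0.69 | 0.701 | 0.549 | 0.709 |
| H. Stable high-risk ATSB children missed 35%, low-risk 5% | 18.3% / 18.3% | 1.00 | 0.876 | 0.999 | 0.879 |

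B and C: both analyses repeat the bias. D: all-negative moves further from the truth. E and F: all-negative shifts although nothing is wrong; the formula agrees, for example 0.699 × 0.908/0.725 = 0.875. G: carry-forward creates bias. H: carry-forward does expose the problem. If pattern B is combined with stable differences in risk between children (frailty variance 1), carry-forward moves only from 0.768 to 0.785 against a truth of 1.00.

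**4. What a tipping-point analysis would show.** First, the plan's own figure. Zambia: 35 per cluster × 70 clusters × 1 year × 0.66 = 1617 person-years against 1610 stated, so 1610/70 = 23.0 per cluster. With rates 0.50 and 0.35, CV 0.40 and 35 clusters per arm, the person-time formula for cluster trials gives 80.4% power against 80% stated. This takes 0.50 as a rate per person-year, although Table 2 gives it per 6-month season.

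SE(log IRR) = √{[1/(0.50×23) + 1/(0.35×23) + 2×0.40²]/35} = √{[0.0870 + 0.1242 + 0.32]/35} = 0.123.

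An observed IRR of 0.70 then has 95% CI 0.55 to 0.89. Let d be the case rate in missed months relative to observed months in the ATSB arm, with the control arm unchanged (d = 1) and the SE held fixed:

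IRR(adjusted) = 0.70 × (1 − m + m·d).

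Significance is lost when d = [1/0.891 − (1−m)]/m.

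| Missing share m | d at which significance is lost | d at which IRR = 1 |
|---|---|---|
| 10% | 2.22 | 5.3 |
| 20% | 1.61 | 3.1 |
| 34% | 1.36 | 2.3 |

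Control-rate scenario at m = 20%: 0.8 × 0.70 + 0.2 × 1.0 = 0.76. With the factor exp(1.96 × 0.123) = 1.273, the 95% CI is about 0.60 to 0.97, still significant. If the control rate is instead read as 1.0 per person-year, SE = √{[0.0435 + 0.0621 + 0.32]/35} = 0.110, the upper limit is 0.869 and the 20% threshold becomes (1/0.869 − 0.8)/0.2 ≈ 1.75.

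**The case against.** These are sensitivity analyses only; the primary analysis invents no outcomes. The plan commits to repeated revisits, to reporting the missing fraction by arm for the intention-to-treat population, and to summarising loss to follow-up by arm and cluster. Unequal amounts of missing data would therefore be visible. This is a master plan, and site-specific plans may modify it. All of that stands and limits the harm. But none of it addresses equal amounts of missing data with unequal content, and the text on the per-protocol set would pass unchanged into the site plans unless someone corrects it.

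A reader might go further and infer that the two analyses can never reveal informative missingness. Pattern H refutes that: carry-forward can pick up missingness tied to a child's stable risk.

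A reader might also see a conflict between carry-forward and the rule that "each positive (treated) participant will have 2 weeks of the following month of observation time subtracted from their at-risk person-time". The plan does not support this, because its carry-forward rule removes follow-up time with each carried case. The real tension is with the confirmation rule for positives in consecutive months.

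It would also be too strong to say that the per-protocol set rests on cluster deployment alone: individual adherence measures and a household-level version are mentioned. What matters is that no version requires complete follow-up.

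**Conclusion.** The point holds in this form: neither planned analysis tests missingness driven by the missed visit's own outcome, and each can hide it or imitate it. For the all-negative analysis this is algebra and needs no assumption about the missingness mechanism. For carry-forward it rests on the assumed patterns in the simulation and on the bypassed confirmation rule. Intention to treat concerns analysis by allocation and gives no warrant for generating cases. The per-protocol conflict follows from the text alone.

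The size is illustrative. At an assumed 20% missing in the Zambia design, with an observed IRR of 0.70, an ATSB-arm rate in missed months about 1.6 times the observed rate removes significance, with the control arm unchanged. The true missing share is unknown. The 20% to 34% loss of person-time in Table 2 is an upper bound for it, because it includes time deliberately excluded after treatment. The roughly 20% under Withdrawal/follow-up counts withdrawals, not person-months. Nothing here shows that the trial's result would be biased; it shows that the plan could not tell.

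**What to change.** 1. Add a delta-adjusted (tipping-point) analysis of the case rate in missed intervals, with the factor varied separately in each arm. Include a scenario in which missed ATSB-arm time carries the control-arm rate, and report the factor at which the confidence interval reaches 1.
2. Drop carry-forward, and delete the sentence presenting it as in keeping with intention to treat.
3. If the all-negative analysis is kept, state that it responds only to the amount missing in each arm, and read it beside the planned by-arm report of missing fractions.
4. Delete the premise that the per-protocol set has full follow-up, so that Missing outcome data agrees with Adherence and protocol deviations and with Analysis populations. Run the same tipping-point analysis on the per-protocol set.

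The cost is SAP wording, carried into the site-specific plans before data lock, and modest programming. No additional data are needed.

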### Missing co-variates

Missing baseline covariates (as defined in the SAP prior to data lock) will be imputed using simple imputation methods in the covariate-adjusted analysis based on the covariate distributions, should the proportion of missing values for a particular covariate be less than 5%. For a continuous variable, missing values will be imputed from random values from a normal distribution with mean and standard deviation calculated from the available sample. For a categorical variable, missing values will be imputed from random values from a uniform distribution with probabilities *P*_1_, *P*_2_, … *P*_k_ from the sample. Seed for the imputation will be pre-set as an 8-digit number based on the date of analysis and documented in all scripts relying on pseudo-random number generators. If the missing values for a covariate are ≥ 5%, then they will be imputed using Markov chain Monte Carlo (MCMC) methods [6].

### Harms

The main risks associated with the intervention are the risk of ingestion of the bait + toxicant by humans, animals, and/or non-target arthropods—particularly the local pollinator insect (bee) population. To mitigate ingestion risk for humans and other mammals bittering agents (Bitrex™) have been added to ATSBs to reduce likelihood of ingestion of ATSBs. Pre-trial studies suggest that interaction between pollinators and ATSBs is insignificant and therefore ATSBs are not a risk to NTOs. As the main harms are not expected to be encountered by study participants there is no formal plan for statistical analyses of harms to study participants. Continued monitoring of trial sites for misuse or product loss will be conducted and these data will be reviewed by the DSMB but they will not be formally analyzed statistically. Unexpected harm may occur during the course of trial and will be considered in reviews and by DSMB though no formal analysis is planned.

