### Secondary objectives

(2)To evaluate the efficacy of ATSB deployment in the context of universal vector control coverage (IRS or LLIN) on community parasite infection prevalence as compared with universal coverage of vector control alone.(3)To evaluate the efficacy of ATSB deployment in the context of universal vector control coverage (IRS or LLIN) on passively detected confirmed malaria case incidence as compared with universal coverage of vector control coverage alone.(4)To assess a minimum set of entomological outcomes (parity, mosquito abundance, human landing rate, entomological inoculation rate) that measure ATSB efficacy in reducing the target vector population and transmission.(5)To assess the acceptability of ATSBs by communities and other stakeholders. This includes the identification of potential barriers to uptake and consistent ATSB coverage, together with an assessment of ATSB impact on coverage and use of existing malaria control interventions (e.g., LLIN use, treatment-seeking behavior).(6)To estimate the cost and cost-effectiveness of deploying ATSBs for malaria control.(7)To assess the safety of ATSBs on humans by monitoring adverse effects in communities where ATSBs are deployed compared to the control.

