### Stopping for harm

The trials do not include formal stopping rules based on harm, because the intervention is not targeted to humans and the expected risk to trial participants is expected to be minimal; thus, formal harm-based stopping rules are not needed. However, this does not preclude the DSMB from stopping the trial for harm should unforeseen consequences of the ATSB or trial procedures lead to harm. For example, deliberate abuse or misuse of the ATSB products or unforeseen non-target insect impacts could lead to harm which causes trial stoppage.

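### Objective 7 promises a human-safety comparison with control, but the SAP specifies no by-arm summary of adverse effects that would answer it

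*SAP article*

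**What the plan says.** Under Secondary objectives, item 7 of the SAP article reads: "To assess the safety of ATSBs on humans by monitoring adverse effects in communities where ATSBs are deployed compared to the control". The objective is explicitly comparative.

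The Harms section names human ingestion first among the hazards: "The main risks associated with the intervention are the risk of ingestion of the bait + toxicant by humans". It then says that the main harms are not expected to fall on study participants, and that for this reason "there is no formal plan for statistical analyses of harms to study participants". Two further statements follow:

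- The only monitoring described is of misuse and loss of the product at trial sites. The section sends the results to the DSMB for review and rules out a formal statistical analysis of them.
- On anything unforeseen: "Unexpected harm may occur during the course of trial and will be considered in reviews and by DSMB though no formal analysis is planned".

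The section Stopping for harm adds that "The trials do not include formal stopping rules based on harm", while leaving the DSMB free to stop a trial for harm.

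**The concern.** A listed objective that compares arms needs at least a defined measure, a denominator and a planned tabulation by arm. Here the section that should supply them says that no formal plan exists. This differs from an article that is merely silent and leaves detail to the protocol, because the SAP takes up harms and states how they will be handled.

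At stake is the status of any safety statement made from these trials. The product holds a toxicant and, in the deployment pattern described in the Introduction, hangs on the outside walls of sleeping structures. The results are meant to support a product dossier and possible referral to the WHO advisory group (Overwhelming benefit rule). The trials are open-label. If the by-arm summary is not fixed in advance, the choice of events, denominator and presentation is left until allocation and results are known.

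**Working it through.** No arithmetic applies. The SAP states no adverse-event rate, detectable difference or precision target for safety, so there is no figure to reproduce. The check is whether any part of the document supplies what objective 7 needs.

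1. **Objective.** Secondary objectives, item 7, asks for adverse effects in ATSB communities set against control. This requires a measure of adverse effects, ascertainment in both arms, and a summary by arm.

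2. **Research questions.** The Secondary research questions run from (2) to (7), and none concerns safety. The objective therefore has no matching question.

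3. **Outcomes.** The secondary outcomes, both where they are listed under Timing of outcome assessments and where they are defined under Analysis, are RDT prevalence, passively detected incidence, parity, mosquito abundance, sporozoite rate, human landing rate and EIR. None is an adverse-event or safety outcome.

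4. **Analysis methods.** The sections from the primary outcome through EIR and the pooled analysis give models or tests for efficacy and entomology only. No safety population, safety denominator or by-arm table of adverse effects is defined.

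5. **Harms section.** It makes three statements, and they do not bear equally on objective 7.
   - The statement on harms to participants (no formal plan) bears directly.
   - The statement on unexpected harm (no formal analysis) bears directly.
   - The statement on misuse and product loss bears little. Those data concern the bait stations, and the Randomization section says control areas receive no sham stations. They have no real control counterpart and could not supply the comparison in objective 7, so declining to test them does not contradict it.

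6. **The reason given.** Low expected harm is a sound reason for having no formal stopping rule and no powered test. It does not follow that nothing need be summarised by arm. The section itself lists ingestion by humans among the main risks. The Overwhelming benefit rule also gives the collection of further safety information as a possible ground for continuing after the efficacy boundary is crossed, yet no plan says how that information would be summarised.

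Read together, objective 7 calls for a comparison and nothing in the document specifies one.

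**The case against.** **Detail may sit elsewhere.** Definition, collection and reporting of adverse events commonly belong in the protocol, which is not shown. The article says each trial will have its own SAP and procedures, and it gives no analysis for the acceptability and cost objectives either. This has weight for definitions and collection. It does not remove the conflict, because on harms the SAP makes an explicit statement, whereas on acceptability and cost it says nothing of the kind. The site-specific SAPs are described as needing only minor modifications, so they are not announced as the place where a harms comparison will be added.

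**Harm is still watched.** The DSMB reviews the monitoring data, considers unexpected harm and may stop a trial. This stands, and it protects participants during the trial. It is not a prespecified by-arm report at the end.

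**A stronger reading.** A reader might infer that the SAP forbids any statistical analysis of harms, so that objective 7 can never be answered. The text does not go that far. It disclaims a formal plan and formal analysis, and descriptive counts by arm are not prohibited. The supportable statement is that no by-arm comparison is specified.

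**A numerical bound.** A reader might also try to show what is lost by taking zero events and the person-years in Table 2 to obtain an upper limit on risk. The documents do not support this:

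- The person-years are on mixed bases. Mali's 3850 matches 38 × 76 × 16/12 = 3851, before the 20% loss. Zambia's 1610 is close to 35 × 70 × 1 × 0.66 = 1617, after the 34% loss.
- The cohorts are children (1 to under 15 years; from 5 years in Mali), whereas objective 7 concerns communities.
- The SAP does not describe adverse-event ascertainment in the cohorts. For the same reason it cannot be assumed that the data needed for a safety table are already being collected.

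**Conclusion.** The concern holds as an internal inconsistency. Objective 7 is comparative, the Harms section declines a formal analysis, and no safety outcome or by-arm summary is found elsewhere in the SAP. Its extent is one listed secondary objective in each of the three trials, and no numerical magnitude can be given from the document. The primary outcome, type I error control and interim rules are untouched.

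The conclusion rests on the SAP article alone. It assumes that the current Harms wording would be followed, and that the site-specific SAPs stay within the minor modifications the article describes. It does not depend on any view of how likely harm is, and it does not say that a hypothesis test or a formal harm stopping rule is needed.

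**What to change.** Reconcile Secondary objectives, item 7, with the Harms section in one of two ways.

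**Option A: keep the comparison and plan it descriptively.** Replace the sentence on participants in the Harms section with text such as: *Adverse effects and human exposure or ingestion incidents recorded under objective 7 will be tabulated by arm and type, with a stated population or person-time denominator. Rates will be given with exact 95% confidence intervals, including the upper bound when no events occur. A rate ratio with a cluster-adjusted 95% confidence interval will be given only where the number of events allows. No hypothesis test will be made.* The denominator and the method of ascertainment in each arm should be named. The remark on unexpected harm should be brought into line.

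**Option B: withdraw the comparison.** If adverse effects are not ascertained comparably in both arms, reword objective 7 as non-comparative safety monitoring with DSMB review, which is what the Harms section now describes.

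**Cost.** Option A adds one descriptive table per trial, provided that adverse effects are recorded in both arms. The SAP does not establish this, so it must be confirmed first. The estimates will be imprecise when events are few, and the report should say so. Option B costs only a change of wording, but the trials could then make no between-arm safety statement. Neither option alters the design, the alpha or the primary analysis.
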